### Procedure and Enrolment

Patients are asked to sign formal consent to participate upon discharge from the ICU. If they confirm their enrolment, they are administered the MMSE [34], the first cognitive assessment (Multimedia Appendix 1). At 6 months, the patients are contacted and administered the telephone-modified version of the MMSE called the Telephone Interview for Cognitive Status (TICS) [35,36] (Multimedia Appendix 2). They also receive the Impact of Events-Revised (IES-R) questionnaire [37,38] (Multimedia Appendix 3) by mail to assess for early symptoms of PTSD [25]. At 12 months after discharge, the patients are contacted, the TICS is administered, and they are mailed the IES-R. The Informant Questionnaire on Cognitive Decline (IQCODE) [37] (Multimedia Appendix 4) is also mailed to their “person responsible” who was identified at the time study recruitment. The hospital outcome assessments are recorded up to one year after discharge from the ICU (Figure 2).

For a pilot study that we conducted in 2011, we followed 8 patients (4 delirium-positive and 4 delirium-negative) for 3 months after their discharge from the ICU. During this time, the design and choice of measurement tools for this investigation were informed.

The questionnaires we employ in this study are well-established and validated in measuring cognition and psychosocial well-being. The MMSE, the most commonly used measure of cognitive function in hospitalized patients [34], is scored from 0 to 30, with lower scores indicating poorer performance. We administer the MMSE for the first time after patients formally consent and at the time of their discharge from the ICU. The TICS is a modified and validated version of MMSE and is administered to the patient over the phone at the 6- and 12-month follow-ups.

The IES-R is a non-diagnostic, self-report measure designed to assess subjective distress for any specific life event. The IES-R consists of the three subscales: hyper arousal, intrusion, and avoidance. These subscales parallel the Diagnostic and Statistical Manual of Mental Disorders IV (DSM-IV) criteria for PTSD. This questionnaire is administered to the patient at the 6- and 12-month follow-ups.

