Patients with a RASS score between –2 and +3 will be administered the CAM-ICU [28]. The CAM-ICU is an adaptation of the Confusion Assessment Method and is widely used for diagnosing delirium with yes and no questions for use with non-speaking, mechanically ventilated patients in the ICU. The study participants are not exposed to any additional testing during their time in the ICU.

Patients assessed as suffering delirium via the CAM-ICU at any time are allocated into the delirium positive study group, while delirium-negative patients are re-tested on a daily basis during the time they remain mechanically ventilated. Those patients who never test positive for delirium are allocated to the delirium-negative group (Figure 1).

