### Measures

This study aims to test the hypothesis that delirium during mechanical ventilation in the ICU promotes long-term cognitive and psychosocial decline and impacts one’s health-related quality of life when compared with non-delirium patients [8-23]. The data recorded at study enrolment, during their stay in the ICU, and at discharge are shown in Textbox 1.

 Data recorded at the time of patient enrolment in the study, during their stay in the intensive care unit, and at dischargeCollected dataAt enrolmentDemographic dataNameMailing addressContact numberDate of birthAgeIndigenous statusSexDate and time of admission to the intensive care unit (ICU)ICU admission diagnosis—Acute Physiology and Chronic Evaluation (APACHE II)Date and time of first intubationDailyRichmond Assessment Sedation Scale (RASS)Confusion Assessment Method for the ICU (CAM-ICU)At discharge from the ICUDelirium positive or negativeDate and time of discharge from the ICUSurvival status at discharge from the ICUMini-Mental State Examination (MMSE)After discharge from the ICU (episode outcome at 6 and 12 months)Survival statusDependency statusCognitive status

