### Sample Size

The primary outcome of this study is the relative decrement in MMSE at 6 months after discharge from the ICU. We used the most relevant clinical trial employing MMSE to quantify cognitive function of both delirium-positive and delirium-negative patients to estimate the expected outcomes for our patients at 6 months after discharge from the ICU in order to make a sample size calculation. We estimated the clinically important reductions expected in MMSE and calculated that, at a type 1 error rate of 5% (alpha .05), we can find the clinically significant difference of 2 points on the MMSE between groups with 80% power if we include a minimum of 81 patients in each group (delirious and not delirious). To allow for potential dropouts following recruitment, we plan to enroll 200 patients.

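### The primary outcome is worded as an MMSE decrement with no stated reference point; the only MMSE follows the delirium exposure, so a decrement taken from it is attenuated and can be cancelled or reversed

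*Protocol article*

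**What the plan says.** **Hypothesis.** Measures: "This study aims to test the hypothesis that delirium during mechanical ventilation in the ICU promotes long-term cognitive and psychosocial decline", compared with patients without delirium.

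**Exposure.** Methods: "Patients assessed as suffering delirium via the CAM-ICU at any time are allocated into the delirium positive study group". Patients who test negative are re-tested daily while ventilated, so group membership is settled before ICU discharge.

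**First cognitive score.** Procedure and Enrolment: "If they confirm their enrolment, they are administered the MMSE [34], the first cognitive assessment", and again "We administer the MMSE for the first time after patients formally consent and at the time of their discharge from the ICU". The textbox under Measures lists no cognitive score at enrolment. Participants excludes people with evident prior decline, but that is a screen and not a measured starting value.

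**Primary outcome.** Sample Size: "The primary outcome of this study is the relative decrement in MMSE at 6 months after discharge from the ICU". It is powered on a 2-point MMSE difference between groups, with 81 per group and 80% power. The starting point of the decrement is not given.

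**Score at 6 months.** Procedure and Enrolment: "At 6 months, the patients are contacted and administered the telephone-modified version of the MMSE called the Telephone Interview for Cognitive Status (TICS"). No MMSE is scheduled at that visit.

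**Pre-ICU reference.** The only one is the informant-rated IQCODE at 12 months, which the Introduction and Procedure and Enrolment describe as looking back to function before the ICU.

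**The concern.** A decrement within a patient needs a starting value, and the schedule offers only the discharge MMSE. That score is taken after the exposure, so it may already carry part of the effect under study. In that role it is an early outcome and not a baseline. Change from it describes the course after ICU discharge, whereas the hypothesis is about decline brought about by delirium in the ICU.

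If delirium lowers the discharge score and the deficit persists, both groups could show the same change while the delirium group remains worse off. If the delirium group starts lower and partly recovers, it could even show the smaller decrement. A true lasting deficit would then be reported as no difference, or as a difference in the wrong direction. Repairing the instrument mismatch at 6 months would not remove this problem, because the starting point would still follow the exposure.

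**Working it through.** **Inputs from Sample Size:** difference 2 points, 81 per group, power 80%, "at a type 1 error rate of 5% (alpha .05"). The number of sides is not stated; two-sided is assumed. No SD is given.

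**Step 1: reproduce 81 per group.** With n = 2 × (1.960 + 0.842)² × SD² / 2², setting n = 81 gives

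SD = 2 × √(81/2) / (1.960 + 0.842) = 4.54.

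So 81 can be back-solved but not verified. A one-sided test would imply an SD of 5.12. An SD of 4.5 gives 80 per group.

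**Step 2: the contrast under a discharge start.** Let G be the shortfall of the delirium group at 6 months and D its shortfall at discharge. The between-group difference in decrement is G − D. Taking the plan's 2 points as G, it is 2 − D.

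**Step 3: power.** Assume the SD of 4.54 also applies to the change. With equal variances this holds when the two scores correlate at 0.5, since the variance of a difference is 2 × SD² × (1 − 0.5) = SD². The standard error is 4.54 × √(2/81) = 0.713. Power in the expected direction is Φ((2 − D)/0.713 − 1.960).

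| Discharge gap D (assumed) | Contrast 2 − D | Result with 81 per group | n per group for 80% power |
|---|---|---|---|
| 0 | 2.0 | power 80% | 81 |
| 0.5 | 1.5 | power 56% | 144 |
| 1 | 1.0 | power 29% | 324 |
| 1.5 | 0.5 | power 10% | 1,295 |
| 2 | 0 | no effect left | none |
| 3 | −1.0 | 29% chance of significance in the wrong direction | none |
| 4 | −2.0 | 80% chance of significance in the wrong direction | none |

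For D = 1: 1/0.713 = 1.40; 1.40 − 1.96 = −0.56; Φ(−0.56) = 0.29.

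**Step 4: sensitivity to the SD.** If the plan's 80% is accepted for a 2-point contrast, the two-sided results do not depend on which SD lies behind it. The ratio 2/SE is then fixed at 2.80, and a contrast of 2 − D has ratio 2.80 × (2 − D)/2. Under the one-sided reading (SD 5.12, standard error 5.12 × √(2/81) = 0.805), D = 1 gives Φ(1/0.805 − 1.645) = Φ(−0.40) = 34% in place of 29%.

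**Step 5: the alternative contrast.** A between-group comparison of 6-month scores that leaves the discharge score out keeps the contrast at 2.0 and, under the same SD, the 80% power.

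**The case against.** Three stronger readings are tempting, and the article supports none of them.

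- *That the plan does measure the decrement from the discharge MMSE.* No section says so. The 2-point difference is stated as one between groups, and Statistical Analysis speaks of comparing mean outcomes in each group. A comparison of 6-month scores is a possible reading, and it subtracts nothing. The reference point may also be defined in a fuller document that is not shown.
- *That the effect will be subtracted out or reversed.* This depends on a discharge gap that the article does not give. With no gap there is no harm, and with a gap below 2 points there is only attenuation. That delirious patients start low and then recover is plausible but not documented.
- *That an analysis of covariance on the discharge score is planned.* Statistical Analysis says only that analysis of covariance will be considered, and it names no covariates. Such an adjustment would not cure the problem, because it conditions on a score taken after exposure: with an assumed slope of 0.5 and D = 2, the contrast would be 2 − 0.5 × 2 = 1.0. There is, however, no stated plan to do it.

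Two further objections have force. Delirium is not randomised, so a 6-month comparison without any pre-ICU score mixes prior differences with decline. And if further decline after discharge were the quantity of interest, a discharge start would be proper, although Measures does not define it that way.

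What remains is that the primary outcome is worded as a change, the only available starting value follows the exposure, and the two readings can give materially different answers. That is more than an omitted detail, since following the wording literally can bias the primary contrast.

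**Conclusion.** The point holds conditionally. The reference for the decrement is not stated, and the only within-patient candidate is a score taken after delirium. If that score is used, each point of delirium-related deficit already present at discharge takes one point off the contrast. With a true 6-month gap of 2 points, a discharge gap of 1 point cuts power from about 80% to about 29%. A gap of 2 leaves nothing to detect, and a larger one reverses the sign.

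These figures assume a two-sided test, a back-solved SD of about 4.5 that applies equally to the change, and discharge gaps chosen for illustration. They show how sensitive the result is and do not predict it. The primary outcome should be clarified before analysis, because the choice affects the direction and meaning of the main result and not only its precision.

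**What to change.** 1. Define the primary contrast as the between-group difference in the 6-month cognitive score, adjusted for variables that precede delirium and are already available: age, sex, APACHE II and site.
2. Name the instrument. As scheduled, the 6-month score is the TICS, so the 2-point MMSE difference and the 81 per group must be restated or justified on that scale, with the assumed SD given.
3. Do not subtract the discharge MMSE or adjust for it in the primary model. Report it as a separate early outcome.
4. Use the 12-month IQCODE, which is already planned, as the supporting measure of decline relative to function before the ICU.

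**Cost.** No new data collection is needed, but the outcome and model wording must change and the sample size must be re-justified for the TICS. Some precision is lost by not conditioning on the discharge score. Residual confounding by unmeasured pre-ICU cognition remains and should be stated as a limitation; the exclusion of patients with evident decline reduces it but does not remove it.

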**Figure 2 figure2:**
[figure not shown]
Assessments after hospital discharge. TICS: Telephone Interview for Cognitive Decline; IES-R: Impact of Events Scale Revised; IQCODE: Informant Questionnaire on Cognitive Decline in the Elderly.

### Measures

This study aims to test the hypothesis that delirium during mechanical ventilation in the ICU promotes long-term cognitive and psychosocial decline and impacts one’s health-related quality of life when compared with non-delirium patients [8-23]. The data recorded at study enrolment, during their stay in the ICU, and at discharge are shown in Textbox 1.

 Data recorded at the time of patient enrolment in the study, during their stay in the intensive care unit, and at dischargeCollected dataAt enrolmentDemographic dataNameMailing addressContact numberDate of birthAgeIndigenous statusSexDate and time of admission to the intensive care unit (ICU)ICU admission diagnosis—Acute Physiology and Chronic Evaluation (APACHE II)Date and time of first intubationDailyRichmond Assessment Sedation Scale (RASS)Confusion Assessment Method for the ICU (CAM-ICU)At discharge from the ICUDelirium positive or negativeDate and time of discharge from the ICUSurvival status at discharge from the ICUMini-Mental State Examination (MMSE)After discharge from the ICU (episode outcome at 6 and 12 months)Survival statusDependency statusCognitive status

### Sample Size

The primary outcome of this study is the relative decrement in MMSE at 6 months after discharge from the ICU. We used the most relevant clinical trial employing MMSE to quantify cognitive function of both delirium-positive and delirium-negative patients to estimate the expected outcomes for our patients at 6 months after discharge from the ICU in order to make a sample size calculation. We estimated the clinically important reductions expected in MMSE and calculated that, at a type 1 error rate of 5% (alpha .05), we can find the clinically significant difference of 2 points on the MMSE between groups with 80% power if we include a minimum of 81 patients in each group (delirious and not delirious). To allow for potential dropouts following recruitment, we plan to enroll 200 patients.

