**Methods:**

This study will be conducted by enrolling patients in two tertiary ICUs in Australia. We aim to recruit 200 patients who have been mechanically ventilated for more than 24 hours. Data will be collected at the following three time points: (1) at discharge where they will be administered the Mini-Mental State Examination (MMSE); (2) at 6 months after discharge from the ICU discharge where the Impact of Events Scale Revised (IES-R) and the Telephone Inventory for Cognitive Status (TICS) tests will be administered; and (3) at 12 months after discharge from the ICU where the patients will be administered the TICS and IES-R tests, as well as the Informant Questionnaire for Cognitive Decline in the Elderly (IQCODE). The IQCODE will be administered to their “person responsible” or the significant other of the patient.

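### The primary outcome and its sample size are set on the MMSE at 6 months, but the cognitive test given at 6 months is the TICS

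*Protocol article*

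**What the plan says.** **Outcome and sample size.** The Sample Size section states: "The primary outcome of this study is the relative decrement in MMSE at 6 months after discharge from the ICU". With the error rate set as "at a type 1 error rate of 5% (alpha .05", it claims that "we can find the clinically significant difference of 2 points on the MMSE between groups with 80% power". The condition attached is that the delirious and the non-delirious group each number 81 or more. It then adds: "To allow for potential dropouts following recruitment, we plan to enroll 200 patients". The stated basis is an earlier study: "We used the most relevant clinical trial employing MMSE to quantify cognitive function of both delirium-positive and delirium-negative patients". No standard deviation is given.

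**Schedule.** The Methods paragraph of the Abstract places the MMSE at the first of three time points, "at discharge where they will be administered the Mini-Mental State Examination (MMSE", and assigns the IES-R and TICS to 6 months. Procedure and Enrolment agrees: "At 6 months, the patients are contacted and administered the telephone-modified version of the MMSE called the Telephone Interview for Cognitive Status (TICS". The legend of Figure 2, which covers assessments after hospital discharge, names the TICS, IES-R and IQCODE but not the MMSE. Textbox 1 under Measures lists the MMSE at ICU discharge and only a generic entry for cognition at 6 and 12 months.

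**Other statements of the primary outcome.** The Results paragraph of the Abstract and the Results section both give a broader primary outcome, covering long-term cognition together with psychosocial function, with no instrument or time point.

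**The concern.** The outcome that sizes the study is expressed on one instrument, and the visit at which it is due uses another. The article names the two tests separately and lists each in its own appendix. It gives the MMSE range (0 to 30) but, for the TICS, no range, SD, important difference or conversion to MMSE points.

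Two things are at stake. First, the text does not define a primary score that the scheduled assessments can supply, and the broader wording in the Abstract and Results does not say which score should take its place. Second, the power claim belongs to a 2-point difference on the MMSE. It does not carry over to the TICS unless the TICS has a comparable important difference relative to its SD, and the article says nothing on that.

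**Working it through.** **Step 1: outcome against schedule.**

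| Place in the protocol article | Cognitive test of the patient at ICU discharge | At 6 months |
|---|---|---|
| Sample Size | not stated | MMSE (primary outcome) |
| Abstract, Methods | MMSE | TICS |
| Procedure and Enrolment | MMSE | TICS |
| Figure 2 legend | not covered | TICS among the instruments listed; no MMSE |
| Measures, Textbox 1 | MMSE | generic cognitive status |

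Only the Sample Size section has an MMSE at 6 months, and no account of the schedule supplies one.

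**Step 2: what the 81 per group implies.** Inputs from Sample Size: difference 2, alpha .05, power 80%, n = 81 per group. Neither the SD nor the sidedness of the test is stated. The usual formula for two means is n = 2(z_alpha + z_power)² SD² / difference². Solved for the SD:

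- SD = difference × √(n/2) / (z_alpha + z_power)
- Two-sided: 2 × √40.5 / (1.960 + 0.842) = 12.73 / 2.802 = 4.54. The t-based version gives 4.52.
- One-sided: 12.73 / (1.645 + 0.842) = 5.12.

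In the forward direction, an SD of 4.5 gives 80 per group by the normal approximation and 80.4, rounded up to 81, by the t-based method. So 81 can be reached with a two-sided test and an SD of about 4.5, but it cannot be confirmed from the stated inputs.

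**Step 3: enrolment.** 2 × 81 = 162 evaluable patients, and 1 − 162/200 = 19%. Enrolling 200 therefore allows for 19% loss.

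**Step 4: the same 81 per group on another scale.** Power = Φ(difference / (SD × √(2/n)) − 1.960), with √(2/81) = 0.1571. The 2-point difference, the SDs and the two-sided test are all assumptions here.

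| Assumed SD | 2 / (SD × 0.1571) | Power with 81 per group | n per group for 80% power |
|---|---|---|---|
| 4 | 3.18 | 88.9% | 63 |
| 5 | 2.55 | 72.1% | 99 |
| 6 | 2.12 | 56.4% | 142 |
| 7 | 1.82 | 44.4% | 193 |

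The t-based powers are within half a percentage point or so of these (88.5%, 71.6%, 55.9%, 43.9%). The table shows how far the answer depends on an SD that the article does not give. It is not an estimate of the study's power.

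**The case against.** The best defence is that the authors regard the TICS as the MMSE by telephone. Procedure and Enrolment describes it as a validated adaptation of the MMSE and speaks of the discharge MMSE as a first administration, which suggests that the 6-month TICS was meant as the repeat. On that view the Sample Size section uses the name MMSE loosely. This may well be the intention, but it does not repair the text: the outcome and the 2 points are stated in MMSE units, and nothing translates them to the TICS.

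The defence does rule out several stronger readings that a reader might infer:

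- **That there will be no primary outcome data.** The documents do not support this. A cognitive score is collected at 6 months; what is missing is a definition that matches it.
- **That two MMSE scores per patient are needed, or that a relative outcome has been sized on an absolute difference.** The phrase can equally mean the shortfall of the delirious group relative to the non-delirious group. This fits the between-group difference in Sample Size and the comparison with non-delirious patients in Measures. The wording is ambiguous, but a contradiction is not established.
- **That 81 is miscalculated or the study underpowered.** Neither is shown. The powers in Step 4 rest on assumed SDs, three of the four above the implied 4.5, on a carried-over difference, and on a two-sided test that the article does not specify.
- **That the analyst will have to choose the outcome after seeing the data.** The analysis plan, the full protocol and the contents of the appendices are not shown, and a scoring or conversion rule could stand in any of them.

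Even such a rule elsewhere would leave the article's own outcome and schedule in conflict.

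**Conclusion.** The primary outcome and its power statement are wrong as written. Sample Size fixes both on the MMSE at 6 months; the schedule gives the MMSE only at ICU discharge and the TICS at 6 months, with no link between the scales. This conclusion rests on the text alone and needs no assumption.

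The consequence for power cannot be given as one figure. It depends on a TICS important difference and a TICS SD that the article does not state. If 2 points were kept and the test were two-sided, 80% power would hold only for an SD of about 4.5 or less; assumed SDs of 4 to 7 span 89% down to 44%. The point must be fixed because it concerns the definition of the primary outcome, but the repair is one of definition and uses data already planned.

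**What to change.** - In Sample Size, replace the MMSE decrement by the TICS total score at 6 months, compared between delirium-positive and delirium-negative patients, as the primary cognitive outcome.
- State the important difference and the SD on the TICS scale, with their source and the sidedness of the test, and restate the power that 81 per group gives.
- Bring the primary outcome wording in the Abstract (Results) and in the Results section into line with this choice, including the place of psychosocial function.
- Keep the discharge MMSE available as a covariate, for which the analysis of covariance already foreseen under Statistical Analysis leaves room. Do not subtract it from the TICS.

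The cost is wording in three places and one recomputed power figure, with no new data collection. The restated power may be less favourable than 80%; if so, the sponsor would have to state the lower figure or revisit the target of 200. Adding an MMSE at 6 months, or adopting a documented conversion between the scales, would also reconcile the text, but the first needs an extra assessment and the second a validated rule that the article does not contain.
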